### Hypotheses and expected outcomes

It is hypothesised that the transformational training program will be superior to care as usual in terms of:

● Organisational strategies to manage depression and BPSD, and

● Staff knowledge and skills in the provision of mental health care;

● Workplace climate factors such as staff trust, teamwork/cohesion, communication and supportive workplace relations;

● Staff factors such as stress, job satisfaction, and turnover; and

● Severity of resident depression and BPSD.

It is also hypothesised that supplementing the transformational training program with clinical support from a mental health nurse specialist will lead to greater benefits than the same program without clinical support.

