## Methods

### Study design

A cluster randomised controlled design will be employed in this study, with participating facilities allocated to one of three conditions. The first condition will implement the training program in six facilities. The second condition will involve the implementation of the training program in another six facilities with the additional provision of clinical support to assist staff in these facilities with the roll out of the strategies and training offered in the program. Clinical support will be provided by an experienced and appropriately trained mental health specialist who will be situated within each facility for approximately one day per week for a six month period. The third condition will include six facilities that will participate in our project as a ‘care as usual’ control group. All participating facilities will be randomly allocated to one of these three conditions, and the control condition will have access to the training program at the end of their participation in the no-intervention condition.

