### Target population

A total of 108 staff will participate in the study, including 54 senior staff (i.e., 3 facility managers and/or RNs from each of the 18 facilities) and 54 senior PCAs (i.e., 3 PCAs from each of the 18 facilities).

A total of 360 residents will be recruited to participate in the study. Across each of the 18 facilities, 10 residents with dementia who present with BPSD will be selected through consultation with facility staff. Similarly, 10 residents with undetected and untreated depression will be recruited across all 18 facilities. Initially depressed residents will be identified through examination of resident files and existing documentation collected for every Australian resident (known as the Aged Care Funding Instrument [ACFI]), which includes a depression screening instrument – the Cornell Scale for Depression in Dementia [14]. However final recruitment will be based on a Research Fellow conducting the Cornell Scale and selecting residents with a Cornell score of 8 and above (must include low mood in symptom count).

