## Results

### Data analysis

For analysis of differences in facilities at baseline, analysis of variance (ANOVA) will be used, with Fisher’s Exact test for analysing categorical variables. For changes over time, repeated measures multiple analysis of covariance (MANCOVA; controlling for group baseline scores on outcome measures) will be used for our continuous measures associated with staff outcomes. Longitudinal Configural Frequency Analysis (CFA) will be used to analyse change in categorical variables such as number of depression and BPSD referrals prior, immediate post training, at 6-month and at 12-month training follow-up. CFA is a technique analogous to repeated measures MANCOVA that allows for the estimation of trends and group differences over time but for categorical variables. Allowing for a 20% attrition rate – a rate of attrition common in our past studies – we have calculated that we will maintain at least 28 staff and 96 residents per condition at 12-month follow-up. Based on our estimated sample size in each of the conditions at 12-month follow-up, and with the expectation of a small-to-moderate effect size d = .20, the power of the analyses for aged care resident data is calculated at 0.99, and for the staff data at .91 at the two-sided significance level of α = .05 for both our mean difference testing and categorical analyses [22].

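### The single resident power figure rests on 96 per condition, which adds two separately recruited samples of 48; on the natural reading each severity outcome has about 48 per condition.

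*Protocol article*

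**What the plan says.** All references are to the protocol article.

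- **Target population.** Two groups are recruited in each facility: "10 residents with dementia who present with BPSD will be selected through consultation with facility staff", and "10 residents with undetected and untreated depression will be recruited across all 18 facilities". Entry to the second group is settled by a Research Fellow "selecting residents with a Cornell score of 8 and above (must include low mood in symptom count". No Cornell threshold is given for the BPSD group. The overall count is "A total of 360 residents will be recruited to participate in the study".
- **Study design.** There are three conditions of six facilities each.
- **Hypotheses and expected outcomes.** The benefit expected for residents is in "Severity of resident depression and BPSD".
- **Evaluation measures for aged care residents.** BPSD severity is measured with the Cohen-Mansfield Agitation Inventory and depression severity with the Cornell Scale. The section does not limit either scale to one group of residents, and does not say that both are analysed in everyone.
- **Data analysis.** "Allowing for a 20% attrition rate", the article states that "we will maintain at least 28 staff and 96 residents per condition at 12-month follow-up". From that count and d = .20 it derives a single power of 0.99 for the resident data at two-sided .05. It gives no count or power for either group.

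**The concern.** A power figure should use the number of people who contribute to the comparison. Residents are recruited for two different problems, and severity is scored on two instruments, one for each problem. If the Cornell comparison concerns residents recruited for depression, and the Cohen-Mansfield comparison those recruited for BPSD, neither has 96 residents per condition.

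Resident severity is one of the stated hypotheses, and the Discussion and Conclusions expect the results to inform service planning and policy. A null severity result read against a claimed power of 0.99 would look like good evidence of no effect. The design could not give such evidence at d = .20. Moreover, a sponsor who corrected the power formula but kept 96 would still credit each severity outcome with about twice its likely sample.

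**Working it through.** **Inputs from the article:** 18 facilities, six per condition; 10 BPSD and 10 depressed residents per facility; 20% attrition; d = .20; two-sided α = .05. **Assumptions made here:** the ICC (.01 to .10) and a comparison of two conditions at one time point.

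**1. The counts reproduce.**
- Total: 18 × (10 + 10) = 360. The stated total works only if the two groups are counted as different residents.
- Per condition: 6 × 20 = 120; after attrition, 120 × 0.80 = 96.
- Per sample and condition: 6 × 10 × 0.80 = 48, so 96 = 48 + 48. Per facility: 10 × 0.80 = 8 of each.

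**2. The stated power does not reproduce from the stated inputs.** For two groups of n, the noncentrality is d × √(n/2), referred to a t distribution on 2n − 2 df.
- n = 96: 0.20 × √48 = 1.386, power 0.28.
- A power of 0.99 at d = .20 needs 919 per condition; 0.80 needs 393.

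**3. The same calculation for one sample, n = 48:** 0.20 × √24 = 0.980, power 0.16.

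| Per condition | Power at d = .20 | d for 80% power | d for 99% power |
|---|---|---|---|
| 96 | 0.28 | 0.41 | 0.62 |
| 48 | 0.16 | 0.58 | 0.88 |

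**4. With clustering.** Six against six facilities, 8 residents per facility in each sample. Design effect = 1 + (8 − 1) × ICC; effective n = 48 / design effect; t on 12 − 2 = 10 df.

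| Assumed ICC | Design effect | Effective n | Power at d = .20 | d for 80% power |
|---|---|---|---|---|
| .01 | 1.07 | 44.9 | 0.14 | 0.66 |
| .05 | 1.35 | 35.6 | 0.12 | 0.74 |
| .10 | 1.70 | 28.2 | 0.10 | 0.83 |

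For comparison, 96 per condition (16 per facility) at ICC .05 has a design effect of 1 + 15 × .05 = 1.75 and power 0.16. Once clustering is counted, going from 96 to 48 lowers power by about 0.04 at that ICC.

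**5. If both scales are analysed in all 96.** Half of the residents were not selected for the symptom being scored. In the limiting case of no effect in that half and an unchanged standard deviation, the average effect is (0.20 + 0)/2 = 0.10, and power at 96 is 0.11. Any benefit in the other half would put the figure between 0.11 and 0.28.

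**6. Can other settings rescue 0.99?**
- A repeated-measures interaction with f = 0.1 (equivalent to d = 0.2 for two groups) and an unstated correlation of 0.7 gives 0.98 to 1.00 at 96 and 0.79 to 0.93 at 48. The same settings give only 0.54 to 0.69 for the 28 staff, against the stated .91.
- Reading .20 as Cohen's f (d = 0.40), with two groups, three measures and correlation 0.5, gives 0.91 at 28 and 0.993 at 48. The article states none of these settings, and this one contradicts its d = .20.

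**The case against.** The strongest reply is that the article never assigns a scale to a sample. Both instruments are listed as resident measures without restriction. The Cornell is a depression scale for people with dementia, and the article says it is among the documentation collected for every Australian resident. Scoring everyone on both scales is therefore compatible with the text, and an article may leave analysis populations to a fuller document. This stands: 48 per outcome is a strong inference, not a stated rule. A reader might infer that the article itself confines each scale to its own sample; it does not.

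Second, the 0.99 is claimed for the resident data in general, including categorical analyses. For referral and file-review outcomes all residents may properly count. This also stands, and the point is limited to the two severity outcomes.

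Third, the check uses a single-time comparison of two conditions, whereas the article plans repeated-measures MANCOVA with baseline control. That model is named for staff outcomes; none is given for continuous resident outcomes. Baseline adjustment would help, but at 96 it would need a correlation of about 0.95 to reach 0.99. The setting at the end of the working also leaves open that the calculation really used 48. If so, the printed text still needs correcting, because it ties the power to 96 and to d = .20.

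Fourth, pooling the two samples is not wrong in itself. An all-resident analysis with recruitment sample as a factor is legitimate if it is stated.

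**Conclusion.** The point holds in limited form. It is certain that 96 is 48 + 48 and that the article attaches one power figure to the combined count. It is a reasonable inference that each severity comparison has about 48 per condition. On that reading, power at d = .20 is 0.16 with independent residents and about 0.14 to 0.10 for assumed ICCs of .01 to .10. Without clustering, the effect detectable with 80% power is 0.58, not 0.41.

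Two stronger conclusions are tempting, and the documents do not support them. One is that the halved sample explains why 0.99 is wrong: the figure already fails at 96 (0.28), so the doubled count is an additional fault. The other is that analysing everyone would necessarily dilute the effect to .10: that is a limiting case, and nothing in the article says that the other half would gain nothing.

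**What to change.** In the Data analysis section, replace the single 0.99 with separate statements for each severity outcome: the number per condition and per facility, and the power or detectable effect. Use 48 per condition (8 per facility) for the Cornell in the depressed sample, and 48 per condition (8 per facility) for the Cohen-Mansfield in the BPSD sample. Give the effect-size metric, the number of measures, the correlation and the ICC behind each figure.

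If all residents are to be analysed on both scales, state that, include recruitment sample as a factor, and justify the effect assumed across a group of which half was not selected for the symptom scored.

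This changes wording only; recruitment and data collection stay as they are. The cost is a less favourable stated figure.

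### The stated power of 0.99 (residents) and .91 (staff) does not follow from d = .20 and the stated numbers; an unadjusted pairwise comparison has 0.28 and 0.11, before any allowance for clustering

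*Protocol article*

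**What the plan says.** The Data analysis section gives a complete set of inputs. After "Allowing for a 20% attrition rate", the authors expect that "we will maintain at least 28 staff and 96 residents per condition at 12-month follow-up". The effect assumed and the resulting figure for residents are given as: "small-to-moderate effect size d = .20, the power of the analyses for aged care resident data is calculated at 0.99". A lower figure applies to the other group of participants, and the error rate is set for both: "for the staff data at .91 at the two-sided significance level of α = .05 for both our mean difference testing and categorical analyses".

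The section names a repeated-measures MANCOVA with baseline adjustment for continuous staff outcomes. It gives no within-person correlation, number of occasions used in the calculation, ICC or design effect. Under Study design the article says: "A cluster randomised controlled design will be employed in this study, with participating facilities allocated to one of three conditions". Each condition has six facilities.

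**The concern.** A standardised difference of 0.20 is small, and 28 or even 96 people per group is few for detecting it. Power of .91 and 0.99 at those sizes is implausible on sight, and a design that randomises whole facilities makes it more so. This is a printed calculation with its inputs beside it, so it can be checked without the full protocol or an analysis plan.

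It is the only justification given for the trial's size. If it is wrong, readers and funders are told that a small effect is almost certain to be detected when it may well be missed. A non-significant result would then look more informative than it is. That bears on the aim, given in the Discussion, of finding out how far external clinical support is needed.

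**Working it through.** **Inputs from the article.** d = .20; two-sided alpha .05; 360 residents and 108 staff recruited (Target population); three conditions of six facilities (Study design); 20% attrition (Data analysis); four measurement occasions (Evaluation measures for aged care staff). Within-person correlations and ICCs below are my assumptions, because the article gives none.

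**1. Retained numbers.** Residents: 360/3 = 120, and 120 × 0.80 = 96. Staff: 108/3 = 36, and 36 × 0.80 = 28.8, taken as 28. These agree with the article.

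**2. Power at the stated inputs.** Two-sample noncentral t, noncentrality δ = d√(n/2), df = 2n − 2.

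- Residents: δ = 0.20 × √48 = 1.386, df 190, power 0.281 (stated 0.99).
- Staff: δ = 0.20 × √14 = 0.748, df 54, power 0.114 (stated .91).

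Comparing two proportions at h = .20 also gives 0.28 and 0.11.

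**3. What the stated power would need.** With d = .20: about 920 residents (for 0.99) or 546 staff (for .91) per condition. With n = 96 and 28: d of about 0.62 and 0.90.

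**4. More generous analyses at d = .20.**

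Both training conditions pooled against control: δ = 0.20 × √(96 × 192/288) = 1.60, power 0.36; for staff, 0.20 × √(28 × 56/84) = 0.864, power 0.14.

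Baseline-adjusted 12-month value: the variance is multiplied by 1 − r². At r = .7 the factor is 0.51, and power is 0.49 and 0.18.

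Baseline-adjusted mean of the three follow-ups, equal correlation r between all occasions: the variance is multiplied by (1 + 2r)/3 − r².

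| r (assumed) | Variance factor | Residents | Staff |
|---|---|---|---|
| .5 | 0.417 | 0.57 | 0.21 |
| .8 | 0.227 | 0.83 | 0.34 |
| .9 | 0.123 | 0.975 | 0.55 |
| .95 | 0.064 | above 0.99 | 0.83 |

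**5. Where .91 could come from.** Read 0.20 as Cohen's f for three groups, with N = 3 × 28 = 84.

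- Group-by-time test, two occasions, ρ = .5: λ = f²Nm/(1 − ρ) = 0.04 × 84 × 2/0.5 = 13.44, F(2, 81), power 0.907.
- Between-group test, four occasions, ρ = 0: λ = f²Nm/[1 + (m − 1)ρ] = 0.04 × 84 × 4 = 13.44, F(2, 81), power 0.907.

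With N = 288 both routes exceed 0.99. But f = .20 is not d = .20. For a between-group effect in three groups it is a range of means of 0.20 × 3/√2 = 0.42 SD (two means equal) to 0.20 × √6 = 0.49 SD (means evenly spaced). For an interaction the gap is also wide: with two groups and two occasions, even f = .10 is a 4 × 0.10 = 0.4 SD difference in change.

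**6. Clustering (assumed ICC, unadjusted).** Design effect 1 + (m − 1) × ICC, with m = 96/6 = 16 residents or 28/6 = 4.67 staff per facility; 12 facilities in a pairwise contrast leave 10 df.

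- ICC .02: design effects 1.30 and 1.073; δ = 1.386/√1.30 = 1.215 and 0.748/√1.073 = 0.722; power 0.20 and 0.10.
- ICC .05: design effects 1.75 and 1.183; power 0.16 and 0.10.
- Difference detectable with 80% power, ICC .02 to .10: 0.51 to 0.71 SD (residents) and 0.86 to 0.97 SD (staff).

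**The case against.** The strongest defence is that the planned staff analysis is not an unadjusted t-test. It uses repeated measures and adjusts for baseline, and with a high enough within-person correlation power rises. The article is also condensed: it cites a source for the calculation, and the correlation, test and any ICC may be in the full protocol.

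Several parts of this stand, and they limit what can be claimed.

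- A reader might take 0.28 and 0.11 as the trial's true power. They are the power of an unadjusted comparison at one time point. No single true power follows from the article, because it states no within-person correlation.
- A reader might conclude that adjustment can never rescue the resident figure. It can at correlations above .9, which is very high and is not stated. For staff, .91 is not reached even at .95.
- A reader might infer that the authors counted four occasions as independent observations. The document does not show this: a two-occasion group-by-time test at ρ = .5 gives the same 0.907. Other inputs come close, such as f = .10 with four occasions (0.88 at ρ = .8, 0.997 at ρ = .9). The route is unknown.
- A reader might think the contrast between training with and without clinical support is the weakest. With equal conditions it has the same numbers as training against control, and no smaller effect is stated for it.
- The ICC values are illustrations. They cannot by themselves show that the stated figures are wrong.

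None of this restores the sentence as written. It gives the effect as d, and 0.99 and .91 do not follow from that effect and those numbers without strong inputs that it does not state.

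**Conclusion.** The point holds in this form: the stated power does not follow from the stated effect size and sample sizes. That rests only on d = .20, the 96 and 28 per condition and two-sided alpha .05, all from the article. Unadjusted pairwise power is 0.28 rather than 0.99 and 0.11 rather than .91. Under the assumed correlations of .5 to .8, adjustment and averaging narrow the gap but do not close it.

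Confusion between d and f is a plausible source, but it is not established. The direction of the clustering effect is certain for any positive ICC; its size is assumed. So the stated figures overstate power for d = .20 under ordinary assumptions, while the exact power of the planned analyses cannot be fixed from this document.

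**What to change.** In the Data analysis section:

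1. Withdraw 0.99 and .91.
2. Say whether 0.20 is d or f.
3. State the test, the number of occasions and the within-person correlation used.
4. Restate power, or preferably the minimum detectable difference, for each pairwise contrast, with six facilities per condition, facility-level degrees of freedom and an assumed ICC range such as .02 to .10.
5. Label which values are unadjusted (the 80% power differences in step 6 of the working are) and which are baseline-adjusted; the latter will be smaller.

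The change is the rewording of one paragraph and a short recalculation. No extra enrolment is proposed. The cost is that the stated power becomes much less favourable.

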### Consent and ethics

All participating aged care staff and aged care residents will be provided with a plain language statement and will be asked to give written informed consent to participate. For staff this will be to participate in the staff training and questionnaire completion. Informed consent to examine resident documentation at the facility and collect outcome data will be obtained from the residents themselves, or if they are unable to provide consent, from their family or guardian. Staff will be paid for both the time spent in the training program as well as for the completion of the questionnaires. Upon completion of the study, participating aged care facilities will receive a plaque and staff members will receive individual certificates. The project has been approved by the Deakin University Human Research Ethics Committee (HEAG- H120_2012 and DU-HREC 2013–013).

## **Discussion**

Organisational barriers clearly limit the effective translation of skills into the routine care practices of staff to address depression and BPSD among residents in aged care facilities. The project described in this article will implement and evaluate two interventions that are designed to address the organisational barriers to mental health care (transformational staff training program and clinical support). It is expected that the project will demonstrate that with the transformational training program, a more accurate identification of depression and the causes of BPSD will ensue, resulting in appropriate treatment being delivered. This will result in less distress and improved quality of life for both residents and staff, and improve the job satisfaction of aged care staff, thereby reducing staff turnover. It will also determine the extent to which external specialist clinical support is required to produce optimal outcomes, an issue that to date has not been clearly determined, and which is essential for appropriate service planning.

## Conclusions

The model for best practice that is identified through this study will provide a framework for the development of training programs for staff to address mental health issues among residents in organisations in a sustainable way. The significance of this project goes beyond the level of individuals and facilities to the broader community. The outcomes from this study will be able to be used strategically to inform policy and practice for improved quality of care of older people with depression and BPSD more generally.
